|----------------------------------|-------------------------------------------------------------------------------------------------------------------------------------------------------------------------------------------------------------------------------------------------------------------------------------------------------------------------------------------------------------------------------------------------------|
| Purpose of clinical trial | To improve prediction of outcomes from surgical intervention in patients with Primary aldosteronism, and evaluate the merits of non-invasive metomidate PET CT versus adrenal vein sampling in the diagnosis of surgically correctable aldosteronism.                                                                                                                                                 |
| Primary objective /aim    | To assess the aldosterone/renin ratio and blood pressure response of patients with primary hyperaldosteronism recommended for surgery or continued medical management following diagnostic testing with 11C-metomidate PET-CT and adrenal venous sampling, and to compare the ability of the two diagnostic modalities to distinguish between unilateral and bilateral aldosterone-producing adenoma. |

|                                            |                                                                                                                                                                                                                                                                                                                                                                                                                                                                                                                                                                                                                                                                                                               |

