## **21.0 Planned Methods of Analysis**

The planned study analyses will be detailed in the study-specific Statistical Analysis Plan (SAP), which will be finalised in advance of study closure.

The primary outcomes will be analysed in a hierarchical manner:

1. Change in ARR, between baseline and 6 months post-surgery (or equivalent time-point relative to baseline if no surgery), comparing patients who have surgery with patients who do not have surgery.
2. Blood pressure cure rates (home SBP < 135 mmHg on no antihypertensive treatment), comparing patients who have surgery with patients who do not have surgery.
3. ARR in patients who have surgery but have discordant AVS and PET-CT results, comparing patients whose surgery was indicated by high probability PET CT with patients whose surgery was indicated by high-probability AVS.
4. Blood pressure cure-or-control rates (home SBP =20 mm Hg or DBP =10 mm Hg lower than prespironolactone/eplerenone, i.e. baseline) in patients with discordant AVS and PET-CT results, comparing those whose surgery was indicated by high-probability PET CT with patients whose surgery was indicated by high-probability AVS.

5. Blood pressure cure rates (home SBP < 135 mmHg on no antihypertensive treatment) in patients with discordant AVS and PET-CT results, comparing those whose surgery was indicated by high-probability PET CT with patients whose surgery was indicated by high-probability AVS.

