## **23.0 Sample Calculation**

The calculations on sample size are based on our stated intention that AVS will only be performed in centres whose robust audit data indicate a bilateral cannulation rate of  $\geq 75\%$ , as the testing of the hypothesis will have maximum clinical value if  $^{11}\text{C}$  metomidate scanning is compared with current best practice AVS. It also assumes that 100% of metomidate scans will provide a technically satisfactory result (we consider this to be reasonable, based on the Cambridge experience since the investigation was first introduced in May 2009).

The design of the study (and therefore the statistical analysis) presupposes that there will be a group of patients for whom the results from metomidate scanning and AVS will differ, but that the former is correct more often and that this difference is statistically significant. Given the results of the proof-of-concept study, it is inevitably the case that there will be a large group of patients for whom the two tests are concordant. The different scenarios of concordant/discordant, unilateral/bilateral, together with their estimated frequencies, are shown in Appendix, and it is these figures that have been used by the Clinical Trials Unit in Glasgow as the model for the sample size calculation and proposed analysis.

Recruitment of 165 patients across 3 centres over 3 years (<1/centre/month), with an estimated 70 proceeding to adrenalectomy, permits 90% power at  $\alpha=0.01$  of detecting non inferiority of PET CT in relation to AVS within a margin 16.7%. Based on the current size of referral practices at each centre, we are confident of meeting the recruitment target.

There will be a sub-study of 6 patients who will have a 11-C metomidate PET CT scan before and following spironolactone/eplerenone therapy. In our previous study, the uptake of metomidate into tumour was 60% greater than contralateral normal adrenal (mean(SD) = 21.7(8.0) vs 13.8 (3.0)). The study of six patients on two occasions will give us 90% power to detect just 30% increase in normal adrenal uptake, even if there is no parallel increase in tumour uptake of metomidate ( $\alpha=0.05$ , one-sample test).

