### **1.2. STUDY OBJECTIVES**

#### **1.2.1. PRIMARY OBJECTIVE**

To determine whether 11C-metomidate PET-CT is superior to adrenal vein sampling in diagnosing unilateral PA, by measuring normalisation of aldosterone/renin ratio and potassium, and change in blood pressure, following adrenalectomy.

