### **2.2.7. MDT DECISION**

MDT decisions (proceed to surgery, or medical management) will be summarised in relation to the diagnosis (BAH, APA, or inconclusive) from each test modality, and combinations of test results (see Section 1.5).

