## **2.3. EFFICACY OUTCOMES**

### **2.3.1. PRIMARY OUTCOMES**

The primary outcomes will be analysed hierarchically. If the first primary analysis is statistically significant at  $p < 0.05$ , then the second primary outcome will be analysed; if the second primary analysis is statistically significant at  $p < 0.05$ , then the second primary outcome will be analysed; and so on. If any primary analysis fails to reach  $p < 0.05$ , then subsequent analyses will be considered secondary analyses.

Each primary outcome will be analysed in the subgroup of FAS patients who undergo surgery.

- Cure of hypertension at 6 months (non-inferiority analyses)
  - comparing accuracy of AVS and 11C-Metomidate PET-CT
  - each scan judged to be accurate if it indicated unilateral disease and cure of hypertension was achieved after surgery, or if the scan did not indicate unilateral disease and cure was not achieved after surgery
  - report estimated difference in accuracy (Newcombe-Wilson method for paired data) between 11C-Metomidate PET-CT and AVS, with 95% CI
  - non inferiority of 11C-Metomidate PET-CT will be declared if the lower limit of the above 95% CI is greater than -17%
  - each measure of cure (see Section 1.8) will be analysed in turn
- Cure of hypertension at 6 months (superiority analyses)
  - in addition to above, report p-value from exact McNemar test
  - superiority of 11C-Metomidate PET-CT will be declared if  $p < 0.05$ , and the lower limit of the 95% CI is greater than 0%

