### **2.3.2. SECONDARY OUTCOMES**

Secondary (and Primary) outcomes will be compared between participants who underwent surgery and those who did not, and for those who underwent surgery, between those for whom surgery was indicated by AVS only, 11C-Metomidate PET-CT only, or both tests.

Linear, binary logistic, or ordinal logistic regression models will be used, as appropriate. Models will be adjusted for age and sex, and the baseline measure of the outcome (where appropriate). To assess differences between those who underwent surgery and those who did not, a categorical variable for whether surgery was performed will be included. To assess differences between AVS and 11C-Metomidate PET-CT, a 3-level categorical variable for whether surgery

was guided by AVS only, 11C-Metomidate PET-CT only, or both tests, will be included.

Similar models will be used to investigate other predictors of outcome after surgery, in the subset of participants who underwent surgery. In line with the secondary objectives, there is particular interest in the following predictors:

- BP response to therapy with spironolactone/eplerenone, measured as:
  - achievement of home SBP <135 mmHg (or clinic SBP <140 mmHg) at week 4
  - achievement of home SBP <135 mmHg (or clinic SBP <140 mmHg) at week 4, without an increase in other BP medication (as per PASO criteria)
  - change in SBP (home SBP if available, or clinic SBP) between baseline and week 4
  - change in SBP (home SBP if available, or clinic SBP) between baseline and week 4, correcting for changes in other BP medication
- Age, sex, ethnicity
- Baseline BP
- Number of classes of antihypertensive medication at baseline
- Tumour genotype, individually and grouping KCNJ5 mutations vs all other mutations
- Tumour immunohistochemical classification
- AVS parameters
  - Contralateral suppression (aldosterone/cortisol in the contralateral adrenal vein < 50% of aldosterone/cortisol ratio in IVC)
  - Contralateral suppression (aldosterone/cortisol in the contralateral adrenal vein < 100% of aldosterone/cortisol ratio in IVC)
- PET parameters
  - number of nodules on each side
  - 'Probability of adrenal adenoma' on contralateral side'
  - SUVmax (TOF) for [hottest] tumour/normal on side of tumour
  - SUVmax (TOF) for [hottest] tumour/liver
  - SUVmax ratio (tumour /contralateral adrenal) using SharpIR;
- 24h-urine steroid profile

Univariate, and multivariable models will be fitted to explore these associations.

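### Protocol section 21 steps 1-2 and the SAP 2.3.2 surgery contrast group patients by operation performed, whereas the protocol objective describes them by recommendation, so patients recommended for surgery but not operated on are never separated.

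*Combined protocol and SAP*

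**What the plan says.** The primary objective in the protocol synopsis, repeated in section 5.2, is to assess ARR and blood pressure response in patients "recommended for surgery or continued medical management following diagnostic testing with 11C-metomidate PET-CT and adrenal venous sampling". It separately asks for a comparison of the two tests. Under section 11.0 the monthly MDT reviews both tests, and surgery is offered if either one indicates unilateral disease.

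The analyses that set operated against unoperated patients use a different grouping:

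- Protocol section 21, steps 1 and 2: "comparing patients who have surgery with patients who do not have surgery".
- SAP 2.3.2: "Secondary (and Primary) outcomes will be compared between participants who underwent surgery and those who did not". The models carry a categorical variable for surgery performed and adjust for age, sex and, where appropriate, the baseline value.
- Protocol section 20.1 and SAP 1.8 give every unoperated patient the same outcome window, 9-12 months after the MDT decision, whatever was recommended.

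The recommendation appears once in the SAP, in section 2.2.7, as a tabulation: "MDT decisions (proceed to surgery, or medical management) will be summarised in relation to the diagnosis".

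The remaining main analyses are built differently. Protocol step 5 is framed as "comparing those whose surgery was indicated by high-probability PET CT with patients whose surgery was indicated by high-probability AVS", and steps 3 and 4 make the same split by indicating test. The SAP primary objective compares PET-CT with AVS "by measuring normalisation of aldosterone/renin ratio and potassium, and change in blood pressure, following adrenalectomy", and SAP 2.3.1 states: "Each primary outcome will be analysed in the subgroup of FAS patients who undergo surgery".

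**The concern.** A patient whom the MDT recommends for adrenalectomy may decline, become unfit, or still be waiting when the outcome is due. In section 21 steps 1-2 and the SAP 2.3.2 surgery contrast, that patient counts as no surgery, alongside patients whose tests pointed to bilateral disease. The comparison group is then a mixture: patients recommended medical management, plus patients with a unilateral result who remained on drugs. The proportions depend on uptake of surgery.

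Uptake may not be random. A footnote to the schedule in section 3.1 says the aim is to discuss the MDT decision with most patients at the visit after four weeks of spironolactone or eplerenone. A patient who has responded well to the drug could be less inclined to have the operation. This is an inference from the timing; the documents do not say it happens.

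At stake is whether the trial reports the response its protocol objective names, and whether the surgery contrast can be read as operated patients against patients recommended medical management. Protocol section 9.2 also says that patients who had both tests enter an intention-to-treat analysis. Neither document defines that analysis by recommendation.

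**Working it through.** **Is there a mismatch, and where?**

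| Place | How patients are grouped | Do unoperated patients enter? |
|---|---|---|
| Protocol objective (synopsis, 5.2) | Surgery or medical management recommended | Yes |
| Protocol 21, steps 1-2 | Surgery performed or not | Yes, pooled |
| Protocol 21, steps 3-5 | Which test indicated the surgery | No unoperated comparator |
| SAP 2.3.1 primary | Paired test accuracy in operated patients | No |
| SAP 2.3.2 surgery contrast | Surgery performed or not | Yes, pooled |
| SAP 2.3.2 indicating-test and predictor models | Operated patients only | No |

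The mismatch lies in the second and fifth rows.

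**How many patients could be affected?**

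Inputs:
- Total recruited: 165 (protocol 12.1).
- Share recommended for surgery: about 50% (protocol 9.0), or the sum of the section 33.0 cells with a unilateral result on at least one test.
- Number operated: 90 (synopsis) or 70 (protocol section 23.0: "with an estimated 70 proceeding to adrenalectomy").

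Section 33.0 cells C+D+G+H+I+J+K+L+M+O+P+Q = 1 + 10 + 1 + 9 + 0.5 + 3.5 + 1 + 29 + 4 × 0.25 = 56%.

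Plan's own figure first: 0.56 × 165 = 92.4, close to the 90 in the synopsis. The 70 in section 23.0 follows from neither share (92.4, or 0.50 × 165 = 82.5).

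Formula: share of the no-surgery group = (recommended − operated) / (total − operated).

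| Total | Recommended | Operated | Recommended, not operated | No-surgery group | Share |
|---|---|---|---|---|---|
| 165 | 92.4 | 90 | 2.4 | 75 | 3.2% |
| 165 | 82.5 | 90 | none (difference −7.5) | 75 | 0% |
| 165 | 82.5 | 70 | 12.5 | 95 | 13.2% |
| 165 | 92.4 | 70 | 22.4 | 95 | 23.6% |
| 149 | 74.5 | 70 | 4.5 | 79 | 5.7% |
| 149 | 83.4 | 70 | 13.4 | 79 | 17.0% |

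The last two rows replace 165 by the 149 completers in protocol section 16.6, which allows for 10% withdrawal.

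The 56% includes 1% with opposite-side results (cells M, O, P, Q), which section 11.0 refers to the Trial Steering Committee. Without them, 0.55 × 165 = 90.75 and the highest share becomes 20.75 / 95 = 21.8%.

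**What it could do to a mean.** The documents give no outcome difference between the two kinds of unoperated patient. As an assumption, if their mean SBP changes differ by 10 mmHg, pooling moves the no-surgery mean by share × 10: 0.3 mmHg at 3.2%, 1.3 at 13.2% and 2.4 at 23.6%.

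**The case against.** Several objections limit the point.

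- **The objective's verb.** For the two treatment routes the objective says assess; compare applies only to the two tests. A reader might infer that the protocol promises a contrast between recommendation groups. It does not. What stands is narrower: the objective describes patients by recommendation, and no outcome analysis reports them that way.
- **Scope.** A reader might also infer that all the analyses pool unoperated patients with the medically managed. The SAP primary analysis leaves them out altogether, and protocol steps 3-5 compare patients by the test that indicated their surgery.
- **The SAP is consistent with itself.** Its secondary objective in 1.2.2 is worded by progression to surgery, which matches 2.3.2. SAP 1.10.3 says its analyses differ from the protocol and that an amendment is planned. The conflict is with the protocol objective, and surgery versus no surgery is only a secondary comparison in the SAP.
- **Built-in limits.** Patients unlikely to proceed with surgery are not recruited (protocol 10.2), and the synopsis lists a new contraindication to adrenalectomy as grounds for withdrawal. Both reduce the number without removing it. Willingness is judged before test results and drug response are known. The SAP defines the Full Analysis Set only by having had both tests, so withdrawal does not by itself take a patient out.
- **The size.** No rate of recommended-but-unoperated patients is stated. The 70 may reflect fewer unilateral results: section 33.0 raised the sample to 165 because of an observed imbalance between the surgical and medical groups. Section 12.1 treats 70 as a minimum and allows for withdrawals before surgery.

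The objection on size stands in full. The upper shares come from subtracting planning figures that disagree with each other, so they bound the problem without estimating it.

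**Conclusion.** The point holds for protocol section 21 steps 1-2 and the surgery contrast in SAP 2.3.2. There, patients recommended for surgery but not operated on join those recommended medical management, no rule separates them, and the MDT decision enters no outcome model. The primary comparison of PET-CT with AVS in the SAP is not affected.

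The size is unknown. It is about 0-3% of the no-surgery group if 90 of 165 are operated on. It reaches 13-24% only if 70 are operated on, nobody withdraws, and the whole gap is non-uptake; with 149 completers that range falls to 6-17%. It would be wrong to conclude that up to a quarter of the no-surgery group will be misplaced, because the documents do not show why the expected number of operations differs between sections.

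This is an inexpensive improvement in how a secondary contrast is reported and in matching it to the protocol objective. It does not invalidate the trial's main analysis.

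**What to change.** In the SAP 2.3.2 surgery contrast, and in section 21 steps 1-2 when the protocol is amended, replace the two-level variable by three levels taken from the recorded MDT decision: operated; surgery recommended but not done; medical management recommended.

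- Report the number in each level.
- Keep the planned as-treated contrast.
- Add a contrast by MDT recommendation, the first two levels together against the third, so that response is reported in the terms of the protocol objective.
- Reconcile the 90 and 70 expected adrenalectomies for the same 165 patients, so that the expected size of the middle group can be judged.

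The cost is SAP wording, one more degree of freedom, and a middle category that may hold only a few patients; if so, describe it without modelling it as a separate group. The MDT decision is already recorded, so no new data are needed and patient care is unchanged.

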### 3.1 Schedule of Assessments and Procedures

| Time Point                 | S
C
R
E
E
N | C-11
Metomidate
PETCT | [18F]CETO
PET CT
**** | A
V
S | B
A
S
E
L
I
N
E | 2wk
Post spiro
50mg | 2wk
Post
spiro
100m
g | MDT**
Meeting
Pts for
surgery
only
continue
to 4
weeks' | 4weeks
post-
surgery | 3
months
post-
surgery | 6months post
surgery

Or 9-12
months after
end of
spironolactone
testing for | 9
month
s | 1-year
post
surgery | 2-year po
surgery |
|----------------------------|----------------------------|-----------------------------|--------------------------------------------|-------------|--------------------------------------|---------------------------|-----------------------------------|------------------------------------------------------------------------------|----------------------------|---------------------------------|---------------------------------------------------------------------------------------------------|-----------------|---------------------------|----------------------|
| Informed consent           | X                          |                             |                                            |             |                                      |                           |                                   |                                                                              |                            |                                 |                                                                                                   |                 |                           |                      |
| Medical history            | X                          |                             |                                            |             |                                      |                           |                                   |                                                                              |                            |                                 |                                                                                                   |                 |                           |                      |
| clinical
examination    | X                          |                             |                                            |             |                                      |                           |                                   |                                                                              |                            |                                 |                                                                                                   |                 |                           |                      |
| Concomitant
medications | X                          |                             |                                            |             |                                      |                           |                                   |                                                                              |                            |                                 |                                                                                                   |                 |                           |                      |
| weight                     | X                          |                             |                                            |             |                                      |                           |                                   |                                                                              |                            |                                 |                                                                                                   |                 |                           |                      |
| Ethnicity                  | X                          |                             |                                            |             |                                      |                           |                                   |                                                                              |                            |                                 |                                                                                                   |                 |                           |                      |
| Inclusion/
Exclusion    | X                          |                             |                                            |             |                                      |                           |                                   |                                                                              |                            |                                 |                                                                                                   |                 |                           |                      |
| Clinic BP/HR               | X                          |                             |                                            |             | X                                    | X                         | X                                 |                                                                              | X                          | X                               | X                                                                                                 |                 | X                         | X                    |

|                                                                                        |   |   |   |   |   |   |  |   |   |   |  |   |   |
|----------------------------------------------------------------------------------------|---|---|---|---|---|---|--|---|---|---|--|---|---|
| Home BP and HR                                                                         |   |   |   | X | X | X |  | X | X | X |  | X | X |
| 12 lead ECG                                                                            |   |   |   | X |   |   |  |   |   | X |  |   |   |
| Dexamethasone
6hrly 3 days prior
to PET CT                                       | X | X |   |   |   |   |  |   |   |   |  |   |   |
| avcs samples.
Aldosterone
cortisol                                               |   |   | X |   |   |   |  |   |   |   |  |   |   |
| Blood tests –
electrolytes with
bicarbonate, urea,
creatinine,
before scan | X | X |   | X | X | X |  | X | X | X |  | X | X |
| ACTH
(before scan)                                                                  | X | X | X |   |   |   |  |   |   |   |  |   |   |
| High-sensitivity
Troponin                                                           |   |   |   | X |   |   |  |   | X | X |  |   | X |
| BNP                                                                                    |   |   |   | X |   |   |  |   | X | X |  |   | X |
| Blood tests –
plasma, renin
activity,
Aldosterone                             | X | X | X | X |   |   |  | X | X | X |  | X | X |
| Renin mass                                                                             |   |   |   | X |   |   |  |   |   | X |  |   |   |
| Serum Cortisol                                                                         | X | X | X |   |   |   |  |   |   |   |  |   |   |
| Pharmacogenetics                                                           | X |   |   |   |   |   |  |   |   |   |  |   |   |
| 24 hour urinary
electrolytes                                                        |   |   |   | X |   |   |  |   |   |   |  |   |   |
| Sodium/potassium                                                                       |   |   |   |   |   |   |  |   |   |   |  |   |   |
| Serum magnesium                                                                        |   |   |   | X |   |   |  |   |   | X |  |   |   |
| Urinalysis                                                                             | X |   |   |   |   |   |  |   |   |   |  |   | X |

|                                              |   |   |   |   |   |   |  |   |   |   |   |   |   |
|----------------------------------------------|---|---|---|---|---|---|--|---|---|---|---|---|---|
| 24hr Urine Steroid Profile                   |   |   |   | x |   |   |  |   |   | x |   |   |   |
| HCG testing for CBP                          | X | X | X | X | X | X |  | X | X | X |   | X | X |
| 2mls sample plasma collected EDTA and frozen |   |   |   | X |   |   |  |   |   |   |   |   |   |
| Serum sample collected spun and frozen       |   |   |   | X |   |   |  |   |   |   |   |   |   |
| CMR surgical***                              |   |   |   | X |   |   |  |   |   | X |   |   |   |
| CMR non-surgical***                          |   |   |   |   |   |   |  |   |   |   | X |   |   |
| QoL Questionnaire                            |   |   |   | X |   |   |  |   |   | X |   |   |   |
|                                              |   |   |   |   |   |   |  | X |   |   |   |   |   |

\*For patients not having surgery next study visit will be 9-12 months and another up to 2 years following MDT review of PET CT/or and Adrenal Vein Sampling

\*\* There will be monthly MDTs, with the aim of having a decision for most patients that is discussed with them at their visit after 4 weeks of spironolactone/eplerenone.

\*\*\* CMR can be done any time before spironolactone/eplerenone treatment and following 6 weeks withdrawal from amiloride, eplerenone and/or spironolactone.

Follow up 6 month CMR scan can be done after 6 month time point but before the 12 month time point. The cohort of n=25 having (18 F) CETO, , 11C-metomidate and AVS no CMR.

[figure not shown]

